## Method

### Design

Figure 1 displays a SPIRIT chart of the
planned study design. The study is a randomized controlled implementation trial
with three parallel treatment arms using a 1:1:1 allocation ratio. A blocked
randomization with blocks of variable length conducted by a random-number
generator (random.org) will be performed. Block length will be determined
randomly (9, 12 or 15 units), before conditions will be randomized within all
blocks separately. An independent research assistant will develop the block list
and conduct the randomization. Patients will be randomized to one of the
following arms: CBT + positive mental imagery induction (PMI), CBT + neutral
mental imagery induction (NMI) and TAU. All arms include an individual CBT
treatment. A cross-therapist design in which any therapist can deliver all three
conditions is applied. Randomization will be focused on patients only, so that
therapists will not see a fixed number of patients per condition. However, we
expect that the block randomization will enable an approximately equal number of
patients in all conditions per therapist. All participants are blind to the
conditions and specific hypotheses. According to the CONSORT statement
concerning the criteria of a pragmatic randomized trial (Zwarenstein et al., 2008) therapists and study coworkers
conducting the information meetings are not blind to allocation. Researchers
involved in data collection and evaluation will be blind to condition labels. An
independent researcher will analyze study data with non-identifying codes of the
conditions. The study includes a longitudinal design with an initial diagnostic
phase (four to five sessions) and the following twelve psychotherapy sessions.
Outcome for the process analysis will be gathered directly after each treatment
sessions. In the intervention analysis, assessments will be made every forth
session: at the start of treatment (pre), after fourth (mid-4), after eighth
(mid-8) and after twelfth treatment session (post-12). In addition, videotapes
of treatment sessions 2, 5 and 8 will be analyzed with an observer rating.

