### Development of the Micro-Interventions

A systematic literature search of interventions to foster PA was conducted,
indicating positive mental imagery as a promising strategy. Important aspects to
boost emotional experiences in imagery interventions were identified based on
relevant studies (e.g. Grol et al., 2017;
Holmes et al., 2008). Procedures of
positive and neutral interventions used in these studies are screened in detail.
Based on this information, we developed a first version of the PMI in a
six-minute format. Next, eleven therapists piloted-tested the intervention with
25 different patients regarding its practical implication. Therapists conducted
the intervention within treatment sessions. An anonymous survey was conducted,
in which patients and therapists described positive and critical aspects of the
intervention independently. We reformulated the intervention script, based on
this feasibility information, to its final version. The NMI script was
parallelized. Scripts for both interventions can be found in the Appendix (see
Supplementary Materials).
We decided to record the interventions on audiotapes that will be played at the
start of each treatment session to increase standardization (inspired by the
PrOMET-study by Mander et al., 2019).
Both interventions are spoken and recorded by UW. The audiotapes will be played
on bluetooth speakers (Anker SoundCore Mini). Two loudspeakers (grey: PMI;
black: NMI) are installed in every therapy room.

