### Conditions and Experimental Session

All three conditions will be parallelized and include a CBT treatment based on an
individual case conception. Every session will start with an initial greeting of
patients and the start of video recording.

Experimental sessions will be conducted from session one to eight in the active
conditions. In each experimental session of the PMI condition, a grey
loudspeaker will be placed on a table in front of patient and therapist with on
average one-meter distance. The therapist will carry out the mood scaling by
asking the patient to rate his/her mood in the present moment from one (very bad
mood) to ten (very good mood). After that, therapists will start the record of
the PMI (duration about six minutes). Patients are guided to imagine a positive
situation from the last week. Directly after the micro-intervention, the same
mood scaling will be conducted again. At the end of the intervention, patients
are instructed to communicate the content of their imagination with their
therapist for about one minute. After completion, the regular CBT session will
begin. After each session patients will complete session questionnaires.
Procedures of the experimental sessions in the NMI condition will be
parallelized to the description above. At session start, the micro-intervention
will be performed with a black speaker with the instruction to imagine a
non-emotional situation within the last week. In the control condition, standard
CBT will be conducted without additional micro-intervention.

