### Study Course From Patients’ Perspective

Figure 2 shows the study course from
patients’ perspective. Patients will get a short-information about the studies
objectives and procedures within in the first session of the diagnostic phase.
If interested, a study coworker will contact them for an additional meeting.
Patients will receive written and verbal study information in this meeting and
will sign informed consent. It will be emphasized that study participation is
voluntary with the option to revoke study participation at any time without
reasons and/or disadvantages. Patients in both active conditions will receive an
introduction to the respective mental imagery intervention, including
cooperative exploration of specific contents (situation imagery as detailed as
possible, sensory modalities, field perspective), examples of positive/neutral
situation in the their life, and a practice of the respective intervention.
Furthermore, possible difficulties with the interventions will be discussed. The
study coworkers will educate patients how to handle it if they fall out of their
imagination during the intervention. After the diagnostic phase, all patients
will run through twelve CBT sessions. Patients will receive session
questionnaires directly after each session. Additional measurements after every
forth session will be included in the study.

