### Bias Minimization

An independent research assistant will randomize patients to treatment arms.
Patients, therapists and researchers involved in the data collection and
evaluation will be blind to the randomization. In addition, patients will be
blind to the specific hypotheses. Patient characteristics will be compared
between conditions to check for possible confounding variables. A
cross-therapist design is applied to minimize therapist effects. The application
of standardized audiotape records will additionally reduce possible therapists
effects. The MLM will decrease an overestimation of effects emerging from the
nested data structure and is robust in handling possible missing data.

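### Patients are declared blind to the conditions, but each patient knows whether an imagery exercise is given and what it contains, so self-rated contrasts with TAU lack the stated protection

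*Protocol article*

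**What the plan says.** The Design section says "All participants are blind to the conditions and specific hypotheses". The next sentence treats therapists and the study coworkers separately: those "conducting the information meetings are not blind to allocation". So the participants in the first statement are the patients.

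Bias Minimization, in the Discussion, returns to the subject. A sentence that begins "Patients, therapists and researchers involved in the data collection and" goes on to say that all these groups are masked to the randomization. It is followed by "In addition, patients will be blind to the specific hypotheses". Patient blinding is thus offered explicitly as a protection against bias.

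The procedures are described elsewhere. Under Study Course From Patients' Perspective, "Patients in both active conditions will receive an introduction to the respective mental imagery intervention", with examples of positive or neutral situations from their own life and a practice run. Under Conditions and Experimental Session, "Patients are guided to imagine a positive situation from the last week" in the PMI arm. The NMI arm is asked for a non-emotional situation, and the TAU arm receives CBT with no micro-intervention.

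**The concern.** Being blind to the conditions would mean that a patient cannot tell which treatment he or she is receiving. Here the treatment is a task that the patient is taught and then carries out, so the statement cannot be literally true of the patient's own procedure.

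This matters because the outcomes are self-ratings of resources, resilience, self-esteem and affect. Knowing that one has, or has not, been given an extra exercise can move such ratings without any change in the underlying construct. A reader who takes the blinding statement at face value would judge the risk of this bias in PMI versus TAU to be low, when the design gives no masking of that contrast.

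**Working it through.** **1. Set the claim against the procedures.** Sources: Study Course From Patients' Perspective; Conditions and Experimental Session.

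| Arm | Before treatment | Sessions 1 to 8 | What the patient necessarily knows |
|---|---|---|---|
| PMI | Introduction, positive examples, practice | Recording asks for a positive situation; mood rated before and after | An exercise is given; its content is positive |
| NMI | Introduction, neutral examples, practice | Recording asks for a non-emotional situation; mood rated before and after | An exercise is given; its content is neutral |
| TAU | No imagery training | No recording | No exercise is given |

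No row is compatible with being unaware of one's own procedure. Two things can still be masked: the specific hypotheses, and which of the two imagery versions is the experimental one.

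**2. Identify who rates the outcomes.** The Measures section describes WIRF, CD-RISC and RSES (primary, intervention analysis) and PANAS (primary, process analysis) as self-reports. The secondary BSI and WAI-SR are self-reports too. The video-based observer rating (ROMA, sessions 2, 5 and 8) is made by independent assistants. It covers resource activation and positive affect, not the three primary intervention outcomes.

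**3. Identify the contrasts affected.** Current Study and Statistical Analysis both hypothesize that PMI exceeds NMI and TAU. In PMI versus NMI both arms have parallel procedures, so that contrast keeps partial protection. In PMI versus TAU one arm has an exercise and the other has none, so patient masking protects nothing.

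**4. Check whether the sample size is involved.** Inputs from the power paragraph under Patients: f = 0.15, 3 groups, 4 measurements, correlation .50, non-sphericity correction 1, α = .05, power .80.

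- Noncentrality: λ = f² × N × m / (1 − ρ) = 0.0225 × 78 × 4 / 0.5 = 14.04.
- Degrees of freedom: (3 − 1)(4 − 1) = 6 and (78 − 3)(4 − 1) = 225.
- Power is 0.801 at N = 78 and 0.795 at N = 77.

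The stated 78 reproduces. The blinding statement does not enter it, so no corrected N follows.

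**5. Illustration only.** The document gives no expectancy effect. Assume no true effect and a pure reporting shift of b SD between two arms. The SD of change is 1, since 2(1 − .50) = 1 with equal variances. Arms have n = 78/3 = 26 or 120/3 = 40. With SE = √(2/n), the two-sided 5% rejection rate is 1 − Φ(1.96 − b/SE) + Φ(−1.96 − b/SE).

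| Assumed shift b | n = 26 (SE 0.277) | n = 40 (SE 0.224) |
|---|---|---|
| 0 | 5.0% | 5.0% |
| 0.1 | 6.5% | 7.3% |
| 0.2 | 11.1% | 14.5% |
| 0.3 | 19.1% | 26.9% |

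The table supports one qualitative statement: a larger sample does not remove the problem. Its percentages are not estimates for this trial.

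**The case against.** Several points on the other side are fair.

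- **Unblinded patients are usual for such interventions.** This stands, and the absence of blinding is not criticized here. The fault is that blinding is claimed.
- **The words may mean something narrower.** Masking to the randomization could refer to concealment of the sequence, and blindness to conditions could mean that patients are not told about the other arms. The first reading is possible for Bias Minimization, but the Design statement names the conditions themselves. If something narrower is meant, the text should say so. Masking to the specific hypotheses may well hold and is not disputed.
- **The neutral arm is already the safeguard.** This largely stands. Current Study gives separating out the specific effect of the affect induction as the reason for two imagery arms. The hypotheses also set PMI against both comparators, although the text does not say that both contrasts must succeed.
- **The observer rating is not patient-rated.** True, and useful for the proposed mechanism, but it does not cover the primary intervention outcomes.

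A reader might infer more than the document supports. One might say that TAU patients know they missed a mood-lifting exercise because "Two loudspeakers (grey: PMI; black: NMI) are installed in every therapy room". Nothing says that the speakers' function is explained to TAU patients, and what the study information discloses about objectives and arms is not shown. For the same reason, it is inference that the purpose of the exercise is obvious to PMI patients, and a flat open-label description of PMI versus TAU claims more than the text settles.

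**Conclusion.** The point holds as a contradiction within the article. The claim that patients are blind to the conditions is incompatible with the described training and sessions, and it is listed as a protection that the design does not have. What remains is, at most, masking to the hypotheses and to which imagery version is experimental.

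The consequence is limited to interpretation. Contrasts with TAU on WIRF, CD-RISC, RSES and PANAS are open to expectancy bias; PMI versus NMI is better protected. The direction and size of any bias cannot be derived from the document.

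It would be wrong to read the illustrative percentages as the trial's false-positive rate. They rest wholly on an assumed shift, and they describe a single two-arm comparison of change. The plan is a three-arm multilevel model with four measurements and hypotheses that also involve NMI. The sample size, the randomization and the choice of outcomes are not called into question.

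**What to change.** 1. In Design and in Bias Minimization, replace the patient-blinding claim. State that patients know whether they receive an imagery exercise and what it contains, and that they are masked at most to the specific hypotheses and to which imagery version is experimental.
2. In Statistical Analysis, state that a claim of a specific positive-affect effect requires PMI versus NMI, in line with the rationale in Current Study. Report PMI versus TAU on self-report outcomes as a comparison not protected by patient blinding, and name expectancy as a limitation.
3. Optionally, add one question to the conclusion survey mentioned under Identification of Risks, asking which version the patient thought was under test. Use it for description only.

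An adjustment for expected benefit is not advised. Measured after the training meeting, it is a post-randomization variable that follows arm-specific content. It may lie on the causal path, so adjusting for it could remove real effect or introduce bias.

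The cost is a few sentences and, if wanted, one survey question. The downside is a less favourable blinding statement.

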### Adherence Strategies

All study coworkers will use standardized materials to enhance adherence.
Patients in both active conditions will be trained in the respective mental
imagery intervention during the diagnostic phase. Patients will get email
address and phone number of the study coworker who conducted the training to be
reachable if any problems or questions occur. Each therapist involved in the
study will be informed about study procedures and technical handling. Further, a
list with the most important study aspects will be handed out to therapists
before enrollment. This list will also be placed in every therapist-office. A
study coworker will regularly contact each therapist in person to enhance study
compliance. Furthermore, data collection will regularly be checked to discuss
irregularities.

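### The pre score of the four-wave intervention analysis is taken after arm-specific imagery training, and the text does not place randomisation or disclosure after consent.

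*Protocol article*

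**What the plan says.** All references are to the protocol article.

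- **Timing of the waves (Design).** Assessments for the intervention analysis are made "at the start of treatment (pre), after fourth (mid-4), after eighth" and after twelfth sessions. The twelve therapy sessions come after a diagnostic phase of four to five sessions. The note to Table 1 calls the pre values baseline scores.
- **Arm-specific training (Study Course From Patients' Perspective).** "Patients in both active conditions will receive an introduction to the respective mental imagery intervention", including work on examples from their own life and a practice run. No counterpart is described for TAU.
- **Timing of that training (Adherence Strategies).** "Patients in both active conditions will be trained in the respective mental imagery intervention during the diagnostic phase".
- **Consent (Study Course).** For interested patients, "a study coworker will contact them for an additional meeting". The section then describes what takes place on that occasion: "Patients will receive written and verbal study information in this meeting and will sign informed consent".
- **Who knows the arm (Design).** Under a pragmatic-trial rationale, "therapists and study coworkers conducting the information meetings are not blind to allocation".
- **Who randomises (Design).** "An independent research assistant will develop the block list and conduct the randomization". The text does not say when, relative to consent.
- **Use of pre (Participants; Statistical Analysis).** Pre is the first of four levels of time in the time-by-condition interaction that was powered, and in the four-measurement multilevel model.

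**The concern.** A baseline should be recorded before anything differs between the arms. Here two of the three arms have rehearsed the tested component, or its neutral parallel, before the reference measurement. The plan's own rationale is that recalling positive personal situations raises positive affect, which then raises resources, resilience and self-esteem. If the practice run does any of this, PMI starts from a raised level and its measured change is too small. No later analysis can recover a clean baseline.

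The second issue is enrolment. The person who explains the study and takes the signature is among those described as unblinded. If that person knew the arm before the signature, the presentation of the study, and the set of patients who sign, could differ by arm. The text neither says this happens nor rules it out.

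**Working it through.** **1. Order of events as written**

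| Step | When | Section |
|---|---|---|
| Information and consent | meeting during the diagnostic phase | Study Course |
| PMI/NMI introduction and practice | diagnostic phase | Study Course; Adherence Strategies |
| Pre assessment | start of treatment | Design |
| Sessions 1 to 12 | after the diagnostic phase | Design; Study Course |
| Randomisation; disclosure to the coworker | before arm-specific training; position relative to consent not given | Design |

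Patients cannot be trained in their own arm's imagery before they have an arm. Randomisation therefore precedes training, and training precedes pre.

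**2. Which analysis is affected**

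The Statistical Analysis section specifies separate models. The process model uses twelve measurements, matching sessions 1 to 12 in Table 1, so pre is not among them. Only the four-measurement intervention model contains pre.

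**3. How much of a lift at pre is lost**

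Let d be a lift at pre in PMI, with the later waves taken as given.

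- Raw pre-to-post contrast: post minus pre, so d is subtracted in full (weight 1).
- Linear slope over the waves coded 0, 1, 2, 3: centred times are −1.5, −0.5, 0.5, 1.5, with sum of squares 2.25 + 0.25 + 0.25 + 2.25 = 5. Pre has weight −1.5/5 = −0.3 in the slope, and 3 × (−0.3) = −0.9 in the fitted total change. The loss is 0.9d.

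**4. The plan's sample size**

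Inputs (Participants): f = 0.15, α = 0.05, power 0.80, k = 3 groups, m = 4 measurements, ρ = 0.50, ε = 1. For the within-between interaction:

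- λ = f² × N × m / (1 − ρ) = 0.0225 × 78 × 4 / 0.5 = 14.04
- df1 = (3 − 1)(4 − 1) = 6; df2 = (78 − 3)(4 − 1) = 225
- power = 0.801, and 78 is the smallest N that reaches 0.80

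The stated 78 is reproduced. With all 120 patients, power is 0.954.

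**5. Illustration of the loss (the share c is assumed; the article gives none)**

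Hold the PMI effect at post fixed and let a share c be present at pre and carried through all waves. A difference that is constant over time belongs to the condition main effect, so the interaction becomes f′ = 0.15 × (1 − c).

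| c | f′ | Power, N = 78 | Power, N = 120 | N for 80% power |
|---|---|---|---|---|
| 0 | 0.150 | 0.801 | 0.954 | 78 |
| 0.1 | 0.135 | 0.696 | 0.895 | 96 |
| 0.2 | 0.120 | 0.575 | 0.798 | 123 |
| 0.3 | 0.105 | 0.448 | 0.664 | 159 |
| 0.5 | 0.075 | 0.232 | 0.357 | 306 |

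A milder version raises pre alone and leaves the other waves of a linear PMI profile (0, 1/3, 2/3, 1) unchanged. For c = 0.2, the sum of squares over time falls from 0.556 to 0.386. Then f′ = 0.15 × √(0.386/0.556) = 0.125, with power 0.616 at 78 and 0.835 at 120.

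**6. Enrolment**

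No arithmetic applies. The consent meeting is run by a coworker, and coworkers who run these meetings are not blind. The independent assistant protects the generation of the list; the text does not say when an assignment is released. The Bias Minimization section does not mention the coworkers. It also describes therapists as blind to the randomisation, which contradicts the Design section and should be reconciled.

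**The case against.** **Enrolment.** A reader might infer that the coworker already knows the arm when asking for consent, so that allocation concealment has failed. The document does not support that. Being unblinded also fits a coworker who is told the arm after the signature in order to give the training. The Study Course section lists consent before the training, and it ties only information and consent to the meeting, so training may be a separate occasion. An independent assistant randomises. Figure 1 (the SPIRIT chart) and Figure 2 (the patient's course) are not available here and may show the order. This stands: the enrolment point is an open risk, not an established fault.

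**Reach.** A reader might also infer that every time-by-condition test is affected, or that pre is spoiled as a covariate. Neither follows. The process model does not contain pre, and no baseline adjustment is described.

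**Size and direction.** One practice run may barely move the outcomes: the article calls resilience a trait, cites a retest reliability of .81 for its scale, and names repetition as important for imagery effects. NMI patients get parallel training, so PMI and NMI differ at pre only through imagery content. A lift in PMI works against the hypothesis and does not create a false positive. All of this is fair and limits the likely size. It does not change the order of events, which puts the baseline after exposure.

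**Conclusion.** The baseline point holds on the text. In the four-wave intervention analysis, pre follows randomisation and arm-specific practice in two of the three arms. A lift confined to PMI is subtracted in full from a raw pre-to-post contrast and at 0.9 from a fitted linear change. The bias is towards missing the hypothesised effect, provided the practice raises scores as the plan's rationale predicts and does so more in PMI than in the comparators. The size cannot be derived from the article. The power figures for c above zero are illustrations on an assumed share, not estimates, and 78 remains correct for the stated inputs.

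The enrolment point holds only in a limited form: an unblinded coworker runs the consent meeting, and the available text does not place randomisation or disclosure after consent. Arm-dependent enrolment is therefore not excluded. If Figure 1 or 2 already shows a protected order, a clarifying sentence would settle this part.

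**What to change.** State and follow this order:

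1. Information and signed consent.
2. Pre assessment of the intervention outcomes (WIRF, CD-RISC, RSES, BSI) and of the baseline predictors, affect and symptom measures (GSE, SUIS, PANAS, SCL-9-K).
3. Release of the next allocation to the coworker by the independent assistant.
4. Imagery introduction and practice for PMI and NMI.

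Add a sentence saying that the coworker learns the arm only after consent and pre data are complete. Place pre and training late in the diagnostic phase, so that few diagnostic sessions fall between pre and session 1. WAI-SR and SACiP-RA refer to a therapy session, so their pre values can be collected after a diagnostic session that precedes disclosure.

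The cost is small: assessments are already computer-assisted, and the diagnostic phase has four to five sessions to work within. Training may need a short separate slot, and pre may fall slightly before session 1. Any change over that gap enters the pre-to-mid-4 interval in all three arms.
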